### Study objectives and hypotheses

This hybrid trial has the following primary objectives:To evaluate the effectiveness and cost-effectiveness of a complex multiple risk intervention on reducing tobacco use, enhancing adherence to Mediterranean dietary pattern and increasing physical activitylevel in 12 months to baseline compared with usual care.To assess the effectiveness of an implementation strategy in terms of acceptability, adoption, appropriateness, feasibility, fidelity, implementation cost and penetration.

Furthermore, other secondary objectives related to the effectiveness of the intervention will also be evaluated: its impact on reducing cardiovascular and depression risksas well as depressive and anxiety symptoms and incidence of major depression.

We hypothesise that the proportion of people who show a positive behaviour change with regard to any baseline behaviours will be higher among people who receive the intervention than people who receive usual care. We also hypothesise that the intervention will reduce cardiovascular risk, incidence of major depression, depression risk and depressive and anxiety symptoms.

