Beginning or making a behaviour change. The proportion of people who are in the stages of action, maintenance or termination according to the TTM at the study entry and at 12 months.Change from baseline on sedentary behaviour. It will be measured by the sitting items from the International Physical Activity Questionnaire.Change from baseline on diet quality. Diet Quality Index-International will be used to determine diet quality [52].Change from baseline on health-related quality of life. It will be measured by the EuroQol-5D questionnaire [53].Reduction of the cardiovascular risk. The proportion of people with low/moderate and high/very high baseline cardiovascular risk who have reduced it. Cardiovascular risk will be calculated using REGICOR [54, 55] and SCORE [56] function charts.Change from baseline on body mass index. Body mass index is defined as the body weight divided by the square of the body height and is expressed in units of kg/m^2^.Change from baseline on waist circumference. The waist circumference will be measured at a level midway between the lowest rib and the iliac crest. It will be expressed in units of cm.Change from baseline on blood pressure. It will be measured in the routine clinical practice by validated electronic monitors and it will be expressed in units of mmHg.Change from baseline on lipid profile. The lipid profile will include: low-density lipoprotein, high-density lipoprotein, triglycerides and total cholesterol. They will be expressed in units of mg/dl.Change from baseline on arterial stiffness. Arterial stiffness will be assessed by the “Cardio-Ankle Vascular Index”. It will be measured by the Vascular Screening System VaSera VS-1500 N or VaSera VS-2000.Change from baseline on theankle-brachial index. It will be measured by the Vascular Screening System VaSera VS-1500 N or VaSera VS-2000.Change from baseline on the “REgicor and Artper Score fOr aNkle brachial index (REASON)” [57].Change from baseline on the perceived functional social support. The questionnaire Duke-UNC-11 will be used to determine the perceived functional social support [58–60].Reduction of the incidence of major depression will be evaluated by CIDI interview [61].Reduction of the risk of depression in participant non-depressed at baseline. Risk of depression will be calculated using the algorithm PredictD [62].Reduction of depression symptoms. The Patient Health Questionnaire-9 will be used to determine the prevalence and the severity of depression symptoms [63].Reduction of anxiety symptoms. The General Anxiety Disorder-7 questionnaire will be used to determine the prevalence and the severity of anxiety symptoms [64].Change from baseline on unhealthy behaviours of professionals of the PHC intervention centres.

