Number in the last 12 months of: hospital care (emergency visits and stays), secondary care (visits to specialists), primary care (visits to physician and nurse), social care services (visits to social worker), outpatient diagnostic tests, medication use, group sessions attended, community resources used and loss of productivity (days off work).	CRF Computerised pharmacy records Electronic health record	External unit of local trained personnel		x		x	
Body mass index, waist circumference, blood pressure and lipid profile	CRF	External unit of local trained personnel		x		x	
Cardiovascular risk	CRF (REGICOR and SCORE function charts)	External unit of local trained personnel		x		x	
Arterial stiffness	CRF (measured by the Vascular Screening System VaSera VS-1500 N or VaSera VS-2000)	External unit of local trained personnel		x		x	
Ankle-brachial index	CRF (measured by the Vascular Screening System VaSera VS-1500 N or VaSera VS-2000)	External unit of local trained personnel		x		x	
Functional social support	CRF (questionnaire Duke-UNC-11)	External unit of local trained personnel		x		x	
Risk of depression	CRF (algorithm PredictD)	External unit of local trained personnel		x		x	
Anxiety	CRF (General Anxiety Disorder-7 questionnaire)	External unit of local trained personnel		x		x	
Depression	CRF (Patient Health Questionnaire-9 and the Composite International Diagnostic Interview	External unit of local trained personnel		x		x	
Appropriateness and acceptability of intervention	Self-administered questionnaire	PHC professionals intervention group			x	x	
Determinants of implementation (CFIR constructs)	Focus group	Research team each autonomous community					x

*CFIR* Consolidated Framework for Implementation Research, *CRF* Case Report Form, *PHC* Primary Health Care

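### The REGICOR/SCORE outcome counts only people whose risk fell, so it cannot show net change in predicted risk or slowed worsening

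*Protocol article*

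**What the plan says.** Under Study objectives and hypotheses the protocol states: "We also hypothesise that the intervention will reduce cardiovascular risk".

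Under Outcomes, i) Effectiveness outcomes, the secondary measure that addresses this is "The proportion of people with low/moderate and high/very high baseline cardiovascular risk who have reduced it". The next sentence names the instruments: "Cardiovascular risk will be calculated using REGICOR [54, 55] and SCORE [56] function charts". The list contains no change in REGICOR or SCORE and no proportion worsened.

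The neighbouring cardiovascular measures are framed differently. Examples are "Change from baseline on blood pressure" and "Change from baseline on lipid profile". Body mass index, waist circumference, arterial stiffness, ankle-brachial index and the REASON score follow the same two-directional pattern.

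Table 4 (Data collection and management) schedules the risk functions, entered as "CRF (REGICOR and SCORE function charts"), at both baseline and the 12-month visit.

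The Analysis section (Effectiveness of intervention) assigns each outcome a hierarchical linear or logistic model for clustered data. A reduced/not-reduced outcome would take the logistic form.

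**The concern.** The hypothesis concerns the level of cardiovascular risk, but the outcome records only one kind of movement. Worsened and unchanged participants are pooled as non-events, so two things are lost.

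- **Direction.** The net effect on predicted risk cannot be read from the result. An intervention that holds back deterioration without moving more people downward would appear to do nothing. Slowed worsening is a plausible form of benefit in a 12-month prevention trial of people aged 45 to 75.
- **Precision.** Turning a score into a yes/no count discards information that the trial has already paid to collect.

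At stake is the interpretation of one secondary outcome. It is, however, the one that speaks most directly to a stated hypothesis.

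**Working it through.** The protocol gives no figure for this outcome, so there is nothing to reproduce. The checks below test what the definition can and cannot show. All shares, means and SDs are assumptions chosen for illustration; none comes from the protocol.

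**1. What the definition can see, with one-step category moves.** Net change per person = share moving up − share moving down. The outcome compares only the shares moving down.

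| Case | Control down / up | Intervention down / up | Outcome: difference in reduced | Net change, control | Net change, intervention |
|---|---|---|---|---|---|
| A | 20% / 30% | 20% / 20% | 0 points | +0.10 | 0.00 |
| B | 20% / 20% | 28% / 28% | +8 points | 0.00 | 0.00 |
| C | 20% / 20% | 28% / 36% | +8 points | 0.00 | +0.08 |

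In case A the intervention prevents a third of the worsening (30% to 20%) and the outcome reports no effect. In case B it reports an 8-point advantage with no net change, and in case C the same advantage with net worsening.

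A difference of that size would probably be declared significant. Inputs from the Sample size section are 140 per centre, 30% loss, 13 centres per arm and an intracluster correlation of 0.01. Completers per centre are 140 × 0.70 = 98. The design effect is 1 + (98 − 1) × 0.01 = 1.97. Effective n per arm is 13 × 98 / 1.97 = 647. Power for 20% v 28% at two-sided 5% is then about 92%. This borrows the planning correlation for an outcome it was not set for.

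**2. The same question if any numeric fall counts.** For a normal change with mean μ and SD σ, P(fall) = Φ(−μ/σ). Take the same mean in both arms, with SD 1.0 in control and 1.5 in intervention.

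- Mean rises 0.5 in both arms: Φ(−0.5/1.0) = 0.309 and Φ(−0.5/1.5) = 0.369. The result is 31% v 37%, an apparent 6-point benefit.
- Mean unchanged in both arms: Φ(0) = 0.50 at any SD, so there is no difference.
- Mean falls 0.5 in both arms: Φ(0.5/1.0) = 0.691 and Φ(0.5/1.5) = 0.631. The result is 69% v 63%, an apparent 6-point disadvantage.

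Wider spread in the intervention arm can therefore push the proportion up, down or nowhere, depending on the sign of the underlying drift.

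**3. Information lost by splitting at zero.** For a small shift in the mean of a normal change, the efficiency of the split relative to the continuous analysis is φ(z)² / [p(1 − p)], where z = μ/σ and p = Φ(−z). This is at the level of the individual, leaving clustering aside.

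- At z = 0 it is (1/2π) / 0.25 = 2/π = 0.637, the best case, with about 36% lost.
- At z = 0.5 it is 0.352² / (0.309 × 0.691) ≈ 0.58, with about 42% lost.

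This applies only if any fall counts. It says nothing about a category-based definition.

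**The case against.** The strongest reply has four parts.

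- **A responder proportion compared between randomised arms is a legitimate secondary outcome** for a hypothesis worded as a reduction. That stands. The proportion is not invalid, but as the only summary of predicted risk it is incomplete.
- **Cardiovascular deterioration is not invisible.** Blood pressure, lipids, body mass index, waist, arterial stiffness, ankle-brachial index and REASON are all followed in both directions. Risk is scored at both visits, and the Analysis section promises descriptive analyses of all variables of interest. This also stands: one cannot say that risk is followed only downward across the trial or that worsening is never counted. The separate measures do not add up to net REGICOR or SCORE risk, however, so the gap in that outcome remains.
- **A reader might infer that the outcome is tilted towards the intervention.** The documents do not support that. They supply no drift, no SDs and no shares, and give no reason to expect both more improvement and more worsening under the intervention. The sign can also reverse, as shown above. Measurement noise affects both arms and does not by itself favour one.
- **A reader might also infer that low/moderate-risk participants cannot succeed, or that two functions without a ranking make the outcome undefined.** Neither follows. The sentence includes low/moderate participants among those who may reduce their risk. It also names four levels in pairs, so a move from moderate to low is possible. The cut-off for a reduction, and how the two functions are ranked or reported, are details that the analysis plan may settle.

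What survives is narrower: the article itself fixes a one-directional summary where a two-directional one is available from the same data.

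**Conclusion.** The point holds in limited form. As written, the REGICOR/SCORE outcome pools worsened with unchanged participants, so it cannot show net change in predicted risk or a benefit that consists mainly of preventing worsening. If change is roughly normal and any fall counts, it also gives up about 36% or more of the information in the continuous change. That figure is conditional on both assumptions.

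Divergence between the proportion reduced and mean risk is a possibility under assumed inputs and can go either way; bias towards the intervention is not shown. The outcome is secondary. The three primary behaviour outcomes and the sample size of 3640 do not depend on it. This is a worthwhile low-cost improvement and does not threaten the trial's main conclusion.

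**What to change.** For REGICOR and for SCORE, add 12-month predicted risk on the continuous scale as a secondary outcome. Compare it by arm in the hierarchical linear model already planned, with adjustment for baseline predicted risk.

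Keep the proportion reduced as a supportive summary. Report it as improved, unchanged and worsened, by arm and by baseline risk group, so that movement in both directions is visible.

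No new data are needed, since Table 4 already schedules both functions at baseline and 12 months. The cost is a change of outcome wording, a little more analysis and one more secondary result per function.

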#### i) Effectiveness outcomes

The effectiveness of the complex multiple risk behaviour intervention in comparison with the usual care at maximum 12 months post-intervention will be measured by:
*Primary outcome measures*
Positive change in baseline eating behaviour: adherence to the Mediterranean dietary pattern in low adherence people. For the evaluation, the 14-item Questionnaire of Mediterranean diet adherence (PREDIMED study) will be used [49]. The positive change has been defined as obtaining eight or fewer points at the study entry and nine or more at the end of the study in this questionnaire.Positive change in baseline physical activity behaviour: sufficient physical activity level in insufficiently active people. For the evaluation, the International Physical Activity Questionnaire will be used [50]. The positive change has been defined as having a low physical activity level at the study entry and a moderate or high physical activity levelat the end of the study.Positive change in baseline smoking behaviour: self-reported continuous abstinence [51]. For the evaluation, the interview will be used and optionally the cooximetry. The positive change has been defined as smoking at the study entry and not smoking at the end of the study. We will measure the punctual and continuous abstinence at these two times.

*Secondary outcome measures*

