### Data collection and management

Data will be collected at PHC centre, professional and participant levels. Data collection methods and procedures are summarised in Table 4.

**Table 4 Tab4:** Schedule of Data Collection Methods and Procedures

			Pre-implementation/Pre-study consent/screening	During implementation			Post-implementation
Activity/Assessment	Data collection	Responsible		Study baseline	Intervention visits	Follow-up 12-months	
PHC centre level							
Characteristics of assigned people	Form report	Research team each autonomous community	x				
Organisational structure	Form report	Research team each autonomous community	x				
Survey of Organizational Attributes for Primary Care	Self-administered questionnaire	Research team each autonomous community	x				x
Professional level							
Age, sex, academic education and experience in PHC	Self-administered questionnaire	Research team each autonomous community	x				
Daily consumption of fruits and vegetables/Level of physical activity/Smoking behaviour	Self-administered questionnaire	Research team each autonomous community	x				x
Appropriateness and acceptability	Self-administered questionnaire	Research team each autonomous community	x				x
Determinants of implementation (CFIR constructs)	Focus group	Research team each autonomous community					x
Participant level							
Informed consent	Paper document	PHC professionals	x				
Age and sex	CRF	PHC professionals	x				
Screening unhealthy behaviours	CRF	PHC professionals	x				
Inclusion/Exclusion criteria	CRF	PHC professionals	x				
Adherence to the Mediterranean dietary pattern	CRF (14-item Questionnaire of Mediterranean diet adherence	External unit of local trained personnel		x		x	
Quality of diet	CRF (Diet Quality Index-International)	External unit of local trained personnel		x		x	
Physical activity behaviour	CRF (International Physical Questionnaire)	External unit of local trained personnel		x		x	
Smoking behaviour	CRF (interview and optional cooximetry)	External unit of local trained personnel		x		x	
Stage of change	CRF	PHC professionals (intervention group)		x		x	
		External unit of local trained personnel (control group)		x		x	
Health-related quality of life	CRF (EuroQol-5D questionnaire)	External unit of local trained personnel		x		x	

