At PHC centre level, we will collect information related to: assigned population (total number; average age; distribution by age group and sex; percentage of immigrants; deprivation index; prevalence of tobacco use; level of physical activity and number of people allocated to home care), organisational structure (population coverage; average attendance; number of physicians, nurses and social workers; accreditation as training health centre; participation in undergraduate and postgraduate training; average visits per day; population per health professional; average time per visit and participation research experience). We will also measure the PHC centres’ internal resources for change by the “Survey of Organizational Attributes for Primary Care” [70].

At the professional level, personal data will be collected (age, sex, academic education and experience in PHC). PHC professionals will have to complete a self-administered questionnaire. This questionnaire collects information about professionals’ behaviours with reference to tobacco use, daily consumption of fruit and vegetables and level of physical activity. In addition only in health professionals of intervention centres, it includes nine items to measure the perception of appropriateness and acceptability of the intervention; these items are based in questionnaires which measure similar constructs [71].

Participant-level data are described in Table 4. Recruitment, first screening for entrance to the study and intervention visits will be done by health professionals. Data collection at participant level will be supported by an external unit of local trained personnel who will carry out two visits (baseline and at the 12 months) in each PHC centre because they are not considered as usual care tasks. Data will be collected by means of an online CRF specially designed for the study. This CRF will be pilot tested in pre-implementation stage (see Table 3). The management of the study is based on a central coordination unit, a regional coordination unit and a PHC coordination unit using different periodic communication methods (meetings, teleconferences, e-mails, etc.).

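### The secondary outcome on professionals' own behaviours is defined in the intervention centres only, so as written it is an uncontrolled before-after change and not a comparison with usual care

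*Protocol article*

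**What the plan says.** In the Protocol article, under Outcomes, i) Effectiveness outcomes, one lead-in covers the primary and secondary measures: "The effectiveness of the complex multiple risk behaviour intervention in comparison with the usual care at maximum 12 months post-intervention will be measured by". The last of the 18 secondary measures is "Change from baseline on unhealthy behaviours of professionals of the PHC intervention centres". It is the only item in the list whose definition names a single arm.

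Under Data collection and management the article states: "PHC professionals will have to complete a self-administered questionnaire". The behaviours are described "with reference to tobacco use, daily consumption of fruit and vegetables and level of physical activity". The next sentence sets an arm limit on a different part of the form: "In addition only in health professionals of intervention centres, it includes nine items to measure the perception of appropriateness and acceptability of the intervention". Table 4 has a professional-level row, "Daily consumption of fruits and vegetables/Level of physical activity/Smoking behaviour", marked before and after implementation.

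Under Analysis, Effectiveness of intervention, hierarchical models for clustered data are planned to estimate the intervention effect on each outcome measure. Under Assignment of intervention, centres are randomised 13 to 13, without concealment at the centres and without blinding.

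**The concern.** The lead-in promises a comparison with usual care, and this item's definition rules one out. Staff behaviour may change between the two surveys for reasons unrelated to the trial: a secular trend, a different season (the article does not tie the two surveys to the same time of year), or the effect of answering the same questions twice. With only the intervention centres in the outcome, any such change is indistinguishable from an intervention effect, yet the result would be listed among the effectiveness findings.

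The population is fixed in the outcome definition itself. An analysis plan that followed it would still leave out the control centres, so this is not a detail merely left to a later document.

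**Working it through.** No figure in the article is at stake. The check is a comparison of the passages, followed by an illustration.

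**1. Can the outcome be read as a comparison?** Let T be the change common to both arms and E the intervention effect. The expected change is T + E in intervention centres and T in control centres. The between-arm difference is (T + E) − T = E. The outcome as defined supplies only T + E: one quantity, two unknowns.

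**2. Can the planned model rescue it?** A hierarchical model for this outcome would have an intercept, an arm indicator, the baseline value and a centre effect. If every professional is in the intervention arm, the indicator is 1 throughout and cannot be told apart from the intercept. No intervention effect can be estimated.

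**3. Are control data planned?**
- *Data collection and management.* The questionnaire sentence names professionals without an arm limit. The next sentence adds nine items for intervention centres only. That contrast makes sense if the behaviour items also go to control centres. This is the natural reading, but it is an inference.
- *Table 4.* The behaviour row carries no arm limit. Nor does the professional-level row for appropriateness and acceptability, although the text restricts those items to intervention centres. An unlimited row therefore does not show collection in both arms.
- *Participants.* Staff of the PHC centres are invited, without an arm limit. This is compatible with collection in both arms but does not state it.

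**4. Illustration (all inputs assumed, none from the article).** Take an unhealthy behaviour with prevalence p0 = 0.30 before and p1 = 0.30 − d after, within-person correlation 0.6, no intervention effect, and a two-sided 5% before-after test on n independent professionals.

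SE² = [p0(1−p0) + p1(1−p1) − 2 × 0.6 × √(p0(1−p0)p1(1−p1))] / n

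False-positive rate = Φ(d/SE − 1.96) + Φ(−d/SE − 1.96)

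Worked case, d = 0.05 and n = 200: SE² = (0.2100 + 0.1875 − 1.2 × 0.1984)/200 = 0.000797, SE = 0.0282, d/SE = 1.77, and the rate is Φ(−0.19) plus a negligible term, about 43%.

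| n | trend 2 points | trend 5 points | trend 8 points |
|---|---|---|---|
| 100 | 8% | 24% | 53% |
| 200 | 11% | 43% | 82% |
| 400 | 17% | 71% | 98% |

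The planned analysis allows for clustering, which lowers these rates. With an assumed 20 professionals in each of 13 centres and an assumed intracluster correlation of 0.05, the design effect is 1 + 19 × 0.05 = 1.95, so 260 professionals count as 260/1.95 = 133, between the first two rows. Clustering changes the standard error only. The bias stays at d.

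**The case against.** The item supports none of the stated objectives or hypotheses, no sample size depends on it, and the article attaches no test or threshold to it. It may have been meant as simple description of intervention staff. That limits the importance of the point but does not remove it: the item stands under effectiveness, beneath a lead-in that promises comparison with usual care, while the article keeps a separate list of implementation outcomes where a one-arm description would fit.

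Three stronger readings are tempting and are not supported.

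- A reader might infer that control data at both times are certain, so that the fix is only a change of wording. Collection in control centres is implied, and a second survey there is not stated.
- A reader might add regression to the mean to the list of biases. Staff are not selected on their behaviour, so it has no evident source here. It would arise only if the analysis were restricted to those unhealthy at baseline, which is not stated.
- A reader might regard a between-arm analysis as free of bias. Participation is voluntary, allocation is open, and the article does not say whether staff joined before allocation was known. Differential participation could bias that comparison too. It would still remove change common to both arms, which the present definition cannot do.

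**Conclusion.** The point holds in a limited form. The definition contradicts its own lead-in, and followed as written it gives a one-arm before-after change from which no intervention effect can be estimated. This rests on the text alone and needs no assumption. That a randomised comparator is already being surveyed is a reasonable inference and not a documented fact.

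The size for this trial is unknown. The error equals whatever change the two arms share, and the rates in the table show only how the problem behaves under assumed inputs. One secondary outcome in staff is affected. The patient outcomes, and the primary conclusions with them, are untouched.

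**What to change.** Redefine the outcome as the difference between intervention and control centres in the change in professionals' tobacco use, fruit and vegetable consumption and physical activity. Analyse it with centre as the cluster and adjustment for each professional's baseline value. Report the change within intervention centres as description only, and state that voluntary participation and open allocation limit the comparison. Say explicitly in Data collection and management, and in Table 4, that control-centre professionals complete the behaviour items at both times.

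If they do so already, the cost is a line of outcome wording, a clarification of the schedule and one additional model. If they do not, a between-arm outcome would need further data collection. The alternative is then to label the item descriptive or move it to iii) Implementation outcomes, so that it is not read as effectiveness against usual care. That costs only wording.
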